### Minimum detectable effect size

2.5

A calculation was carried out to estimate the effect size the trial could detect as statistically significant. Cohen's d was used as an effect size measure. As an outcome variable, the *Teacher-Rated Strengths and Difficulties Questionnaire* (SDQ) total difficulties score at first post-assessment was considered.

For calculating the minimum detectable effect size (MDES) we considered two scenarios. For the first, we took into account the matched-pair design. However, as our matching criteria had presumably only weak associations with the outcome variable, the MDES calculations were also performed using simple cluster random assignment. In both cases, we used a significance level of 0.05 and a power value 0.8; average class size was an estimated 20 children. For the first scenario an intra-cluster correlation coefficient (ICC) of 0.15 was assumed for children in the same pair of schools. The effects of the pairs of schools were treated as random - with random intercepts and random effects on intervention. To account for intervention effect heterogeneity values of 0.5 and 0.75 were employed as a ratio of the variance of the intervention effect between pairs to the variance between pairs. On these conditions, 21 pairs with one intervention and one control school resulted in a MDES of 0.257 (or 0.286 if the random effects variance ratio was 0.75). Adding covariates to the children level (i.e. gender and baseline score) with an assumption of 20% variance reduction decreased the MDES value to 0.243 or 0.273.

With the second scenario, we discarded the level of pairs and assumed an ICC of 0.15 for children in the same school. The ICC for the primary outcome measure was based on earlier research in the field [32], [33]. The effects of the schools were considered as random intercepts. With 42 schools randomized to the intervention or control groups on a 1:1 bases, this scenario resulted in a MDES equal to 0.389. Again, adding children-level covariates (assuming a 20% variance reduction) diminished the MDES, yielding 0.380.

In other school-based intervention trials, the effects on students' mental health and well-being were found to vary between small and moderate [34]. Previous trials of GBG have found the effects on students behavior also to vary between small and moderate [35], [36]. Based on the calculations, we are aware that statistical power is an issue with this trial and we might be able to detect moderate effects.

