**Child-completed assessments**				
Response inhibition (Go/No-Go task)		X	X	

During the 1st year the teachers from intervention classes receive training as well as regular mentoring hence the first post-test demonstrates the effects following active implementation. Previous trials have showed that the immediate effect of GBG will be measurable by the end of 1st year, while follow-ups have found continuing positive effects of the intervention even if the intervention is not implemented after first year [54]. There is no cut-off for intervention during the study period, but as the teachers do not receive regular implementation support during 2nd academic year, the implementation of the intervention may decline during that time. The rationale for second post-test is to find out if the intervention has long-term effects, which will be measurable regardless if teacher's use or don't use the intervention.

First post-test is given priority in determining the intervention effects. The control group will not receive the intervention until the second post-testing in May 2018 has been completed.

Teacher's fill out SDQs for each child taking part in the study and the teacher's questionnaire (containing teacher's background information, TSES and the classroom behavior measure) during all three assessments. Paper versions of the questionnaires are sent to schools by NIHD.

Parents fill out electronic or paper versions (according to their preference) of parental questionnaires (containing sociodemographic, SDQ and SNAP-IV data) also three times. Electronic parental questionnaires are sent to parents via email. Paper versions are sent through schools and parents return filled out questionnaires to the NIHD in prepaid envelopes.

Subgroups of children complete computerized Go/No-Go tasks twice - in October 2016 and May 2017.

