
### Statistical analysis plan

2.10

Demographic and baseline characteristics at the pupil level will be summarized using means and standard deviations (or medians and inter-quartile ranges) for continuous variables and percentages for categorical characteristics.

For analyzing the intervention effects on child outcomes, two scenarios are presented. First one will be used when matching has been effective (correlation between paired cluster response means (SDQ total difficulties) at baseline is at least moderate i.e. above 0.4) and takes into account the matched-pair design. Multilevel linear models with three levels (child, school, and pair) will be used with continuous responses (i.e. SDQ total difficulties mean score at post-test), where intervention group (PAX GBG vs. control) will be entered at the school level as a fixed effect, random effects will model differences between pairs and variation of the intervention effect among pairs. Covariates (i.e. gender and pre-intervention score) will be included at child-level. Binary outcomes (i.e. SDQ bandings no risk/at risk) will be compared between trial arms using multilevel generalized linear models. Even though pair-matched cluster randomized trials have analytical limitations, the focus of analysis will be on the overall effect of intervention, which can still be estimated [55].

Second scenario will be used when matching has been ineffective (i.e. correlation is small). As suggested by research [56], [57], breaking pair matches and treating the design as completely randomized might be useful strategy. Two-level hierarchical linear models (child, school) will be used with continuous responses and Generalized Estimating Equations (GEE) with the ‘sandwich estimator’ for robustness for binary responses. This approach will help to find out if and how many children will transit from ‘at risk’ to ‘no risk’ banding.

Multilevel models will use maximum likelihood estimation to handle missing data, assuming that data is missing at random [58]. GEE requires stronger assumption of missing data mechanism and assumes data is missing completely at random.

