Secondary analysis will seek to find out whether the intervention has effect on child's inhibitory control and on symptoms of ADHD. Differences from baseline to post-assessment between the two trial arms will be estimated using multilevel models, including child-level covariates (i.e. baseline response inhibition/baseline ADHD score and gender). Analyzing the intervention effects on teachers will be conducted with same scenario as the effects on children. Two level models will be used to take into account the pair-matched randomization and linear regression when matching has not been effective. Teacher's gender, age and years of experience teaching will be added as teacher-level covariates.

Explanatory analysis will be conducted to examine potential moderators of intervention effects. The aim is to find out if the intervention has different effect to children based on their baseline risk-status (i.e. no risk vs. at risk on SDQ) and socio-demographic factors (i.e. family structure and socioeconomic status), using four-level (with pair-matched design) or three-level (when matching was ineffective) models with repeated measures entered as first level variables. Secondary analysis about the effects to child's inhibitory control and to teacher's self-efficacy as well as explanatory analyses are purely exploratory, with any significant findings needing to be replicated in other studies as the power of these analyses is low.

Intervention fidelity will be reported descriptively.

Analysis will be made without multiplicity adjustments as the main purpose is to compare intervention and control group using a single primary variable. Secondary objectives are adding to the value of the intervention and supporting the hypothesis relating to the primary variable (positive effect on children's mental health).

Impacts are estimated on the basis of modified intention to treat (mITT) [59], excluding randomized schools deemed ineligible immediately after randomization. Even though this type of estimation can introduce bias [60], it is believed that excluding two randomized schools as well as their matched participants from the analysis is sensible. Thus, data is collected from 42 schools and analysis will be based on their input.

Trial reporting will follow the CONSORT guidelines [61].

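### The main outcome models are in effect complete-case, so maximum likelihood does not deal with missing scores in the way the plan says

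*Protocol article*

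**What the plan says.** Section 2.10 of the protocol article sets out two scenarios for continuous child outcomes.

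- **Matching effective:** "Multilevel linear models with three levels (child, school, and pair) will be used with continuous responses (i.e. SDQ total difficulties mean score at post-test"; intervention arm is a fixed effect at school level, and pairs have random intercepts and random intervention effects.
- **Matching ineffective:** "Two-level hierarchical linear models (child, school) will be used with continuous responses".
- **Baseline:** "Covariates (i.e. gender and pre-intervention score) will be included at child-level".
- **Missing data:** "Multilevel models will use maximum likelihood estimation to handle missing data, assuming that data is missing at random".

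Repeated measures appear in one place only, the exploratory moderator analyses, which are run "using four-level (with pair-matched design) or three-level (when matching was ineffective) models with repeated measures entered as first level variables".

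Section 2.9.3 settles the time point: "First post-test is given priority in determining the intervention effects". Its schedule collects teacher-rated SDQ, parent-rated SDQ and SNAP-IV at all three waves, and the Go/No-Go task at the first two.

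**The concern.** Likelihood estimation makes use of an incomplete child through that child's other observed responses. The main models give each child a single response and treat the baseline score as a fixed covariate, so an incomplete child has nothing left to contribute. The missing-data sentence therefore describes a property that these models, as specified, do not have.

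Two things are at stake. First, children whose outcome was observed leave the analysis because a baseline form is missing. Second, a reader will take the missing-at-random statement to be conditional on the data the trial collects, when it is conditional only on what is in the model. The second post-test and the other raters' scores are not in it.

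**Working it through.** **1. Is there an occasion level in the main models?** The main models have three levels (child, school, pair) or two (child, school). The moderator models, with repeated measures at level 1, have four or three. The difference is exactly one level in each scenario. The article counts occasion as a level when it uses one, and it does not count one in the main models. No imputation and no model for the baseline score is stated.

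**2. What does a maximum likelihood fit of the stated model use?** The two-level model was fitted to one simulated data set of 42 schools × 20 children = 840.

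- Post-test missing: 119. Baseline missing: 57. Both missing: 10.
- Children with both scores: 840 − 119 − 57 + 10 = 674. The fit used exactly these 674. The estimate and log-likelihood were identical whether the full file or the complete-case file was supplied.
- Dropped despite an observed post-test: 840 − 119 − 674 = 47.
- With baseline as a response, 840 − 10 = 830 children and 1680 − 119 − 57 = 1504 scores would enter, although a child with a baseline score alone says little about the arm contrast.

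**3. Does this bias the estimate?** The check used 2000 simulations with a true effect of −0.30, generalised least squares with known variance components, and a Monte Carlo standard error of about 0.003.

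| Data analysed | Post-test loss | Mean estimate |
|---|---|---|
| Full data | none | −0.306 |
| Complete cases, loss depends on baseline and arm | 20% | −0.306 |
| Complete cases, loss depends on arm and an observed variable outside the model | 22% | −0.198 |

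The third row was built to be unfavourable: the outside variable tracks the post-test closely and drives loss in the control arm only. It shows the direction of the risk and does not forecast its size.

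**4. How many children are affected?** No missing rates are given, so these are assumed and taken as independent across waves. With baseline missingness m0 and post-test missingness m1, the share analysed is (1 − m0)(1 − m1), and the share dropped despite a post-test is m0(1 − m1).

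| m0 | m1 | Analysed | Dropped despite post-test |
|---|---|---|---|
| 5% | 5% | 90% | 5% |
| 10% | 20% | 72% | 8% |
| 20% | 25% | 60% | 15% |

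**5. What does it cost in precision?** Section 2.5 gives the inputs: "we used a significance level of 0.05 and a power value 0.8; average class size was an estimated 20 children", an ICC of 0.15, 21 pairs or 42 schools, heterogeneity ratio 0.5 or 0.75, and a 20% child-level variance reduction (R²). The test is taken as two-sided, with M(df) = t(0.975, df) + t(0.80, df), so M(20) = 2.946 and M(40) = 2.872.

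- Matched: M(20) × √{[ratio × ICC + 4(1 − ICC)(1 − R²)/(2n)]/21}. With ratio 0.5, R² = 0.20 and n = 20: 2.946 × √[(0.075 + 0.068)/21] = 0.243.
- Unmatched: M(40) × √{4[ICC + (1 − ICC)(1 − R²)/n]/42}. With R² = 0.20 and n = 20: 2.872 × √[4(0.15 + 0.034)/42] = 0.380.

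All six published values are reproduced: 0.257, 0.286, 0.243, 0.273, 0.389 and 0.380. Replacing n = 20 by the number of complete children per class, with covariates:

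| Lacking either score | n | Matched, 0.5 | Matched, 0.75 | Unmatched |
|---|---|---|---|---|
| 0% | 20 | 0.243 | 0.273 | 0.380 |
| 5% | 19 | 0.246 | 0.276 | 0.382 |
| 10% | 18 | 0.249 | 0.279 | 0.384 |
| 20% | 16 | 0.257 | 0.286 | 0.389 |
| 30% | 14 | 0.267 | 0.294 | 0.395 |

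Full recovery of every child who has a post-test (n = 20(1 − m1) in place of 20(1 − m0)(1 − m1)) moves the unmatched figure from 0.384 to 0.382, 0.394 to 0.389 and 0.403 to 0.392 for the three rows of step 4.

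**The case against.** **Complete-case is not the same as invalid.** With one response per child, the complete-case likelihood is the observed-data likelihood when only the post-test is missing. If loss depends on arm, gender and baseline score, given school and pair effects, the estimate is sound, as the second row of step 3 shows. This stands. A reader might infer that the missing-at-random statement is empty, or covers only gender and baseline. Neither is supported, because arm, school and pair are also in the model.

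**The primary outcome is the least exposed.** The class teacher rates every consenting child at each wave, normally stays with the class (section 2.6.2), and completed the baseline ratings blind to allocation (section 2.9.3). If a whole school leaves, section 2.4 drops its pair, and neither proposed model changes that. This also stands. Parent forms, which have to be returned by each family at each wave, are the likelier place for gaps.

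**Power is barely touched.** Correct. The article admits that power is an issue, and a reader might infer a serious further loss. Step 5 does not support that, because between-school variance dominates.

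**An article leaves detail to the full plan.** Full-information likelihood with modelled covariates would make the sentence true, and a plan not shown might specify it. But the article fixes the response, the covariates and the levels and then claims a property for that model. The mismatch is in what is stated. The sentence is right for the repeated-measures moderator models.

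**Baseline-adjusted analysis of one post-test is conventional.** So it is, and it could be kept with imputation or with an accurate description.

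**Conclusion.** The point holds for the continuous-outcome main models in both scenarios. As specified, maximum likelihood recovers no child with an incomplete score, and any child with a post-test but no baseline score is dropped. It does not extend to the moderator models.

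The consequence is limited. The estimate remains valid under a narrower assumption than a reader would suppose: post-test loss depending only on arm, gender and baseline score, given school and pair effects. Precision loss is small across the assumed range: with 5% to 30% of children lacking either score, the covariate-adjusted minimum detectable effect rises by 0.003 to 0.024 (matched, ratio 0.5) or 0.002 to 0.015 (unmatched). Bias arises only if loss also depends on information outside the model, and its size cannot be judged from the document. No alternative model makes missing at random true; it can only make the assumption more plausible by conditioning on more of what was observed.

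These figures rest on assumed missing rates, independence across waves for the step 4 shares, and the inputs of section 2.5.

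**What to change.** For the continuous child outcomes, do one of the following.

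1. Enter the baseline and post-test scores (both post-tests where collected) as responses in one multilevel model with occasion at level 1, then child, school and, if retained, pair. Constrain the arm means to be equal at baseline and take the arm contrast at the first post-test as primary.
2. Keep the present model and multiply impute missing baseline and post-test scores with a multilevel imputation model that includes arm, the other waves and the other raters' scores.
3. If neither is wanted, describe the main analysis as complete-case, report the number of children excluded by arm, and state the narrower assumption.

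The second option is the more direct way to bring in other raters' scores; the first uses only other waves of the same measure. The cost is revised wording, modest programming and a slightly more complex model, with no new data. The benefit is keeping children with observed outcomes and a more plausible missing-at-random assumption, mainly for the parent-rated SDQ and SNAP-IV.

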### Design

2.1

This study is an ongoing pragmatic, two-year, cluster-randomized waitlist-controlled trial conducted during school years, 2016/17 and 2017/18, in Estonia. One first grade class from each school among 42 schools participates in the study. Fig. 1 outlines the participant flow.

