**Teacher-rated assessments**				
Background variables		X	X	X
Child's mental health and prosocial skills (SDQ)		X	X	X
Teacher's sense of efficacy (TSES)		X	X	X
Classroom behavior		X	X	X

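### The teacher-outcome models list gender, age and experience as covariates but not the baseline score of the same outcome, which is collected and would add precision at almost no cost

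*Protocol article*

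**What the plan says.** Section 2.10 (Statistical analysis plan) gives the form of the teacher models: two-level models that reflect the pairs, or linear regression if matching proves ineffective. It then says that the teacher's "gender, age and years of experience teaching will be added as teacher-level covariates". No baseline value of a teacher outcome is named.

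The baseline values exist. Section 2.9.3 says that teachers complete the questionnaire containing "TSES and the classroom behavior measure) during all three assessments", and Table 1 schedules both measures at baseline and at both post-tests. Section 2.9.3 also states that participants were blind to allocation at baseline, and section 2.4 says schools were told the result only after baseline collection.

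The child models are specified differently. In section 2.10 the three-level model for continuous child outcomes adjusts for gender and the pre-intervention score. The models for inhibitory control and ADHD symptoms adjust for the baseline value of that outcome and gender.

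Teacher efficacy and classroom behaviour are both secondary objectives in section 2.9. Section 2.10 calls the teacher self-efficacy analysis purely exploratory because its power is low; it does not name the classroom-behaviour measure in that statement.

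**The concern.** The teacher analyses have the smallest number of units in the trial: "One first grade class from each school among 42 schools participates in the study", so there is one class teacher per school and at most 42 in all. In a sample that small, a baseline measurement of the same outcome is usually the most obvious candidate for adjustment. The plan uses such adjustment where it lists covariates for child outcomes, yet for teachers it lists three background variables only.

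What is at stake is precision. If a teacher's baseline rating predicts the later one to any useful degree, leaving it out makes the confidence intervals for two secondary outcomes wider than the collected data require.

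**Working it through.** **Step 1. Reproduce the plan's own MDES figures (section 2.5).** The inputs are "we used a significance level of 0.05 and a power value 0.8; average class size was an estimated 20 children"; for the second scenario the authors "assumed an ICC of 0.15 for children in the same school". The design is "With 42 schools randomized to the intervention or control groups on a 1:1 bases".

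- Second scenario: MDES = (t₀.₉₇₅,₄₀ + t₀.₈₀,₄₀) × √(4 × (ICC + (1 − ICC) × c/20)/42), where c = 1 without covariates and c = 0.8 with them.
- Multiplier: 2.021 + 0.851 = 2.872.
- c = 1: 2.872 × √(4 × 0.1925/42) = 2.872 × 0.1354 = 0.389, as stated.
- c = 0.8: 2.872 × √(4 × 0.184/42) = 2.872 × 0.1324 = 0.380, which agrees with "adding children-level covariates (assuming a 20% variance reduction) diminished the MDES, yielding 0.380".
- First scenario, 21 pairs: (t₀.₉₇₅,₂₀ + t₀.₈₀,₂₀) × √((w × 0.15 + 4 × 0.85 × c/40)/21). With w = 0.5 this gives 0.257 (c = 1) and 0.243 (c = 0.8); with w = 0.75 it gives 0.286 and 0.273. All four match.

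The plan's figures therefore use two-sided 0.05 and t multipliers. The same conventions are carried to the teacher outcomes, for which the article states no MDES.

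**Step 2. Teacher outcomes without the baseline score.** Linear regression on 42 teachers, 21 per arm, with intercept, arm and the three listed covariates leaves 42 − 2 − 3 = 37 degrees of freedom. The noncentral-t multiplier for 80% power is 2.877.

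MDES = 2.877 × √(4/42) = 2.877 × 0.3086 = 0.888 SD.

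The SD here is the one remaining after gender, age and experience.

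**Step 3. Teacher outcomes with the baseline score.** One more covariate leaves 36 degrees of freedom, with multiplier 2.879. If ρ is the baseline-to-follow-up correlation after the listed covariates, then MDES = 2.879 × √(4 × (1 − ρ²)/42). The article gives no ρ, so a range is shown.

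| Assumed ρ | Residual variance removed (ρ²) | MDES (SD) | Power at d = 0.5 | Equivalent unadjusted teachers, 42/(1 − ρ²) |
|---|---|---|---|---|
| not adjusted | – | 0.888 | 35% | 42 |
| 0 | 0% | 0.889 | 35% | 42 |
| 0.3 | 9% | 0.85 | 38% | 46 |
| 0.5 | 25% | 0.77 | 44% | 56 |
| 0.6 | 36% | 0.71 | 50% | 66 |
| 0.7 | 49% | 0.63 | 60% | 82 |

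**Step 4. Cost if the baseline score turns out to be uninformative.** At ρ = 0 the MDES moves from 0.888 to 0.889. Allowing for chance imbalance in the extra covariate (variance factor 1 + 1/36) makes it about 1.5% worse.

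**The case against.** The strongest counter-argument is textual. Section 2.10 says the teacher analysis follows the same scenario as the child analysis and that the teacher covariates are to be added. One could read this as the child specification, baseline score included, plus three more covariates. But the scenarios in that section are defined by whether matching was effective, and the sentence after the cross-reference applies exactly that split to teachers. The natural reading concerns model levels, not covariates. If carry-over was meant, it still needs saying.

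A second objection is that the article's covariate lists are condensed. A reader might infer that every child model adjusts for baseline and the teacher models alone do not. The text does not support that. The pre-intervention score is named for the first-scenario continuous model and, as the baseline value, for inhibitory control and ADHD; the second-scenario models and the binary models list no covariates. The contrast holds only for child models that list them.

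Third, the gain rests on an unknown correlation. This stands. At 0.3 the MDES falls by only about 5%. Section 2.9.2 says nothing is known of the validity or reliability of the four-item classroom measure, and its baseline was taken early in first grade, so a high correlation cannot be presumed.

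Fourth, self-efficacy is declared exploratory, and even at ρ = 0.7 power at d = 0.5 is only 60%. This also stands and limits the importance of the point, though low power is itself a reason to take an inexpensive gain.

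Two further inferences should be resisted. A reader might conclude that age and experience duplicate each other, so one should go; the article gives no figure on this, and one covariate costs next to nothing. A reader might also want a pair term in every teacher model; the plan provides for linear regression without pairs when matching is ineffective, and nothing here argues against that.

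**Conclusion.** The point holds as a matter of precision. The stated covariate list for the teacher models leaves out a pre-allocation-disclosure measurement of the same outcome that the trial collects. Under the assumptions of 42 teachers with complete data, 80% power and two-sided 0.05, this leaves the MDES at about 0.89 SD, where adjustment would give about 0.85 to 0.63 SD for assumed correlations of 0.3 to 0.7. The gain is modest at the lower end, clear from 0.5 upward, and practically free if the correlation is near zero. Missing questionnaires would raise all these figures.

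A reader might infer that chance baseline differences in self-rated efficacy invalidate the comparison. They do not: randomization keeps the estimate without baseline adjustment unbiased, and such differences are already reflected in its standard error. The primary outcome is unaffected. The correction is worth making but concerns secondary outcomes, one of them explicitly exploratory.

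**What to change.** In section 2.10, add the baseline value of the same score (the TSES subscale or the classroom-behaviour measure being analysed) to gender, age and years of experience in each teacher-outcome model. Apply this both to the two-level model and to the linear regression, so that the matching rule stays as it is. If baseline adjustment was already intended through the cross-reference to the child analysis, one sentence saying so is enough.

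The cost is one sentence and one degree of freedom per model; the data are already in the collection schedule.
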